### Sample size

Based on the sample calculation for each aim, we will recruit a minimum number of subjects needed to conduct all aims. Thus, 208 participants (n=104 per primary group) will be recruited. *Alpha level setting:* The primary groups (DHA+EPA vs. placebo) share 3 post-heading time points (1^st^ 24h, 2^nd^ 24h, 168h), which will be compared to the pre-heading baseline. Thus, we set the alpha level at 0.017 to account for multiple comparisons. Based on the estimated effect sizes and alpha level, a sample size of 90 (Aim 1), 74 (Aim 2), and 82 (Aim 3) per primary group will result in 90% power to detect the supplementation effect. We accounted for a dropout rate of 15%, resulting in n=104 per group needed to accomplish all aims.

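### With 15% dropout, 104 per group leaves about 88 and not the 90 stated for 90% power in Aim 1; the effect on power is under one percentage point

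*Protocol article*

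**What the plan says.** All the figures are in the Sample size section of the protocol article. The evaluable numbers for the three aims are given as "a sample size of 90 (Aim 1), 74 (Aim 2), and 82 (Aim 3) per primary group will result in 90% power", with the significance level fixed by the statement "we set the alpha level at 0.017 to account for multiple comparisons". The recruitment target is "208 participants (n=104 per primary group) will be recruited". The link between the two is a single sentence: "We accounted for a dropout rate of 15%, resulting in n=104 per group needed to accomplish all aims".

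The section does not print the inflation formula. It refers to estimated effect sizes without giving any, and it names neither the test used for sizing nor whether the alpha is one- or two-sided.

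**The concern.** The section presents the recruited number as the minimum that serves every aim once 15% are lost. A reader will take this to mean that, if 15% drop out, each aim still has its required number. For Aim 1 that is not so: 15% off 104 falls short of 90.

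Aim 1 sets the size of the trial, so its calculation has no slack, whereas Aims 2 and 3 ask for fewer participants. What is at stake is whether the stated combination of 208 enrolled, 15% dropout and 90% power is true, and how far off it is if not.

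**Working it through.** **Inputs (all from the Sample size section).** Evaluable n per group: 90 (Aim 1), 74 (Aim 2), 82 (Aim 3). Power 90%. Alpha 0.017. Dropout 15%. Recruited: 104 per group, 208 in total.

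**Step 1: reproduce the printed 104.** There are two candidate formulas, n x (1 + dropout) and n / (1 - dropout), each rounded up.

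| Aim | n needed | n x 1.15 | n / 0.85 |
|---|---|---|---|
| 1 | 90 | 103.5, so 104 | 105.9, so 106 |
| 2 | 74 | 85.1, so 86 | 87.1, so 88 |
| 3 | 82 | 94.3, so 95 | 96.5, so 97 |

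Only Aim 1 with multiplication gives 104, and the match is exact. Aim 1 therefore drives the figure.

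**Step 2: apply the stated dropout to the stated enrolment.**

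- Remaining per group: 104 x 0.85 = 88.4, about 88, against 90 needed.
- Remaining in total: 208 x 0.85 = 176.8, against 180 needed.
- Enrolment that keeps 90: 90 / 0.85 = 105.9, so 106 per group and 212 in total, four more than planned. Check: 106 x 0.85 = 90.1.
- Dropout that 104 can absorb: (104 - 90) / 104 = 14 / 104 = 13.5%.

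This step needs no effect size, variance or choice of test.

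**Step 3: size of the power loss.** The article gives no effect size, so this step rests on assumptions: a two-sided two-sample t-test at alpha 0.017, and a standardised difference d back-solved so that the stated n gives 90% power.

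A normal approximation shows the route. With z(0.9915) = 2.387 and z(0.90) = 1.282, d = (2.387 + 1.282) x sqrt(2/90) = 0.547. At 88 per group, d x sqrt(88/2) = 3.627, and power is Phi(3.627 - 2.387) = 0.893.

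The t-test version for Aim 1 is below. Required sizes are usually rounded up, so the unrounded requirement behind 90 could be anything just above 89. The table shows both ends.

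| Unrounded n behind the stated 90 | d | Power at 88 | Power at 88.4 |
|---|---|---|---|
| 90 | 0.551 | 89.2% | 89.4% |
| 89.01 | 0.554 | 89.6% | 89.8% |

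Aim 1 power at 15% dropout is therefore about 89.2% to 89.8%. Sidedness hardly matters: under the normal approximation, power at 88 per group is 0.8926 two-sided and 0.8932 one-sided.

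**Step 4: the other aims at 88 per group.** The same method gives d = 0.609 and power 94.7% for Aim 2, and d = 0.578 and power 92.2% for Aim 3. Both stay above 90%.

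**The case against.** The best case on the other side accepts the arithmetic and disputes its weight.

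- **Size.** The gap is two per group and less than one power point. The 15% is itself a planning guess, and the design tolerates 13.5%. This stands, and it is why the point is minor.
- **The formula is inferred.** The article never says how the allowance was applied. A reader might take multiplication as established. The exact match makes it likely, but the text does not confirm it. The shortfall in Step 2 does not depend on the cause.
- **Completers are not the analysed sample.** The Primary analysis section plans a mixed model for repeated measures, with the primary time point 24 hours after heading. A participant lost after that visit still contributes primary data, and the article does not say when the 15% is expected to occur. This could soften the shortfall. It does not remove it, because under Trial design the heading measurements follow 8 weeks of supplementation. Someone lost in those weeks has neither a pre-heading nor a post-heading outcome for the model to use, and nothing says that the 15% excludes such losses.
- **The power figures rest on assumptions.** True, and for that reason they are given as a range.

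It is also no answer that a fuller document may exist. The article prints both the inputs and the result, and they disagree with each other.

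**Conclusion.** The stated figures conflict: 90 needed, 15% dropout and 104 sufficient cannot all hold. This is certain, since it follows from the printed numbers alone. That the allowance was multiplied on (90 x 1.15) and not divided out (90/0.85) is the likely explanation, but it is an inference.

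The consequence is minor: two participants per group, and Aim 1 power of about 89.2% to 89.8% in place of 90%, given the assumed two-sided t-test and the back-solved effect size. Aims 2 and 3 are not affected.

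A reader might infer that the trial is materially underpowered or must enrol more. The figures do not support that. The loss is under one percentage point, it applies only if dropout exceeds about 13.5%, and it reaches only the one aim without slack.

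**What to change.** Keep enrolment at 208 and correct the sentence in the Sample size section. It should say that 104 per group gives 90% power for Aim 1 with up to about 13.5% dropout (14 per group), and about 89% at 15%, with Aims 2 and 3 above 90% in both cases. The sponsor should replace the 89% with the value from its own effect size and test.

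The cost is one sentence and a slightly less favourable power statement. Design, analysis and recruitment do not change. If the sponsor prefers to keep the claim of 90% power at 15% dropout, the matching figure is 106 per group, 212 in total, which is four more participants. The small gain in power does not make that necessary.

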## Discussion

NF-L, tau, and S100B have been shown to reflect the severity of cellular damage ranging from acute subconcussive head impact/concussion [6,10,59] to neurogenerative diseases [60,61]. We recently showed that GFAP and UCH-L1 were elevated during a high school football season, and UCH-L1 had significant associations with the extent of brain tissue strain [62]. An interaction between omega-3 FAs and axonal integrity was suggested by Oliver et al.[31] and Heileson et al.[30] in which omega-3 FAs pretreatment in college football players minimized the elevation of NF-L, while groups given placebo continued to show elevated NF-L levels in concert with subconcussive head impact exposure throughout the season. We postulate that DHA will protect the integrity of neural cellular phospholipid membrane, by which cellular enzymatic and structural proteins remain intact even after acute soccer headings, as well as 2 sessions of cumulative subconcussive head impact exposure. If this hypothesis is supported by the blood biomarker data coupled with other measurements, this highlights a novel preventive strategy of DHA+EPA for subconcussive neural injury. It is possible that some biomarkers may increase after headings in both groups, the panel of biomarkers assessed reflect diverse aspects of neural health, such as axonal structure, neuronal protease system, and astrocyte activation. Our data analysis will determine whether DHA+EPA can act to protect all or only specific aspects of neural health.

Our pilot data [63] combined with published concussion studies [64,65] suggests that DTI and NODDI can detect both acute and long-term axonal microstructural damage. We postulate that DHA+EPA pretreatment will enhance cellular and physiological resilience to acute subconcussive impacts. Diffusion metrics may reveal microstructural integrity while the connectivity analysis depicts functional connectivity between brain regions. Using DTI/NODDI/fMRI as outcomes for omega-3 FA research, we predict significant changes in axonal diffusion measures after 20 acute headings in the placebo group and that damage will be attenuated in the DHA+EPA group. The fMRI data will indicate whether structural damage resulted in neurophysiologic abnormalities. If notable association between multimodal imaging metrics are present, the data will be useful in understanding the physiology of DHA and EPA’s protective effects.

Our data will provide mechanistic insights as to how acute subconcussive head impacts induce sympathetic hyperreactivity. A meta-analysis concluded that DHA and EPA supplementation (3-4g/day) results in a decrease in blood pressure [25], which can be modulated by both autonomic and vascular origins. DHA+EPA supplementation (3.4g/d) for 8 weeks has been shown to lower sympathetic reactivity and attenuate the MAP response during the CPT [27]. Acute subconcussive head impacts have been shown to negatively influence autonomic function by triggering sympathetic hyperreactivity. We predict that 8 weeks of DHA and EPA pretreatment will prevent sympathetic hyperreactivity and attenuate the rise in MAP during the CPT not only after a single session of soccer headings, but also after 2 sessions. If our hypothesis is confirmed, DHA and EPA have a potent protective function for the autonomic nervous system against repetitive subconcussive head impacts.

The results obtained from this study will be valuable insights into combined effect of DHA and EPA on brain molecular, cellular, and physiological health in the context of subconcussive head impacts. Furthermore, these findings will pave the way for a large-scale longitudinal randomized clinical trial, serving as empirical evidence to inform the development of preventative guidelines for athletic organizations.

### Patient and public involvement

It was not appropriate or possible to involve patients or the public in the design, or conduct, or reporting, or dissemination plans of our research.
